## Abstract

Vertigo and dizziness are amongst the most common symptoms in medicine and often have a major impact on activities of daily life. Although many causes of vertigo and dizziness can easily be recognized, patients often receive inappropriate and ineffective treatment. The reasons for this are various. Because vertigo/dizziness is an interdisciplinary symptom and there is a lack of standardised diagnostic tools, it is easy to lose the overview of the possible differential diagnoses. There is evidence though, that the management of patients with vertigo/dizziness can be optimized using standardized care pathways with digital support. The present study (within the framework of “PoiSe—prevention, online feedback, and interdisciplinary therapy of acute vestibular syndromes by e-health”) aims to evaluate the implementation of a program with several interlocking components. The three main components are a computerized clinical decision system, a mobile application, a counselling and interdisciplinary educational program developed by the German Center for Vertigo and Balance Disorders (DSGZ). The study is a cluster-randomized controlled trial with a parallel-group design, as well as a detailed process evaluation. Clusters comprise of primary care physician practices in Bavaria, Germany. In the scope of the study the effectiveness, acceptability and efficiency of the intervention will be evaluated. It is anticipated that the intervention will improve the quality and efficiency of the management of dizzy patients. A higher diagnostic accuracy, optimized treatment, and disease progression monitoring is expected to improve patient-relevant outcomes and reduce health-care costs.

## Background

Vertigo and dizziness are amongst the most common key symptoms in medicine. Lifetime prevalence has been shown to lie between 20 and 30% [1, 2]. Claims data from the Bavarian Statutory Health Insurance Physicians’ database showed that over 9% of the adult population received a diagnosis of vertigo annually, most of these in primary care [3]. Disorders of the central or peripheral vestibular system may lead to severe permanent disability or to considerable restrictions of daily life [4]. Although most syndromes—as a rule—can be correctly diagnosed and managed by specialists with interdisciplinary training [5], there is still a large discrepancy between recommended and actual management of patients with vertigo [6, 7]. This might lead not only to overuse of health care resources [4, 8], but also to a prolonged clinical course and to the development of chronic complaints or somatization. Notably, primary care physicians perceive diagnosis and treatment of vertigo as complex and challenging while they feel that they risk missing life-threatening conditions such as stroke or neoplasms [7]. Also, while monitoring symptom evolution under treatment, which is of the utmost relevance for the disease management, it has been noted that the resources of a typical primary care consultation are too limited to closely monitor patients with vertigo. Likewise, the narrow view of single aspects of the underlying disorders reflects the compartmentalization of the clinical specializations (neurology, otorhinolaryngology, internal medicine, etc.) with non-uniform clinical guidelines, and insufficient interdisciplinary cooperation [9].

To overcome these problems of management, monitoring and lack of interdisciplinary consultation, various computerized solutions have been proposed. Computerized clinical decision support systems (CCDS) are technologies that aim to optimize clinical decision-making in situations of uncertainty and complexity [10]. Evidence for their effectiveness has been shown for care process parameters such as the ordering of diagnostic tests [11] or medication prescription. Evidence for their effectiveness on patient-reported outcomes, however, is still limited [12]. Secondly, various mobile solutions for the management of chronic disease and risk factors, e.g. for type 2 diabetes [13], bipolar disorders [14], headache [15] or congestive heart failure [16] that have the potential to facilitate monitoring therapy adherence and success are currently being developed. Thirdly, in remote rural areas tele-medicine applications are increasingly used to support primary care decisions with expert advice (e.g. in stroke [17] or emergency medicine [18]; for review see [19]). All these solutions are often implemented as isolated interventions without overarching concept of care and without dedicated evaluation of the implementation processes and their barriers.

We therefore hypothesized that a combination of CCDS with an easy-to use mobile application and systematic expert support would be able to improve diagnostic accuracy and outcomes of patients presenting with acute vertigo syndromes in primary care, if supported by a large network of different stakeholders.

The objective of this study is therefore to evaluate the implementation of an innovative program with several interlocking components. Specifically, we want to examine the effectiveness, acceptability and efficiency of the new program in primary care.

## Methods

The study protocol follows the Standard Protocol Items: Recommendations for International Trials (SPIRIT).

### Trial design

The present study is a cluster-randomized controlled trial with a parallel-group design (PG-CRCT), including a 6-month pilot phase. A detailed process evaluation alongside the trial will be carried out.

Clusters will be primary care practices in Bavaria, one of Germany’s 16 federal states with a population of about 13 millions. Clusters will be randomly assigned in a balanced 1:1 block design to either the intervention or the control group after inclusion into the main study. Concealed allocation of participating practices will be implemented centrally by an independent person that has no knowledge of the practice identity. The randomization sequence will be computer-generated. The size of the practice (number of patients per year) will be considered as a stratification factor. Practices with special focus on vestibular or balance disorders will be excluded.

The study will be submitted to the local ethics committee for approval and prospectively registered in the German Clinical Trials Register (DRKS) before inclusion of the first patient.

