### Participants

*Clusters* Practices in Bavaria will be eligible if they are led by at least one primary care physician and have patients insured by the Allgemeine Ortskrankenkasse Bayern (AOK Bayern), one of the largest health insurance funds in Bavaria with approximately 4.5 millions insured patients. As insured patients are entitled to freely choose their physician and some patients might directly consult medical specialists, neurologists, otorhinolaryngologists and internal medicine specialists will be included in addition to family practitioners.

*Patients* Consenting patients will be eligible for inclusion if they newly consult a participating practice for acute vertigo or dizziness (ICD-10 codes (H81.1–H81.3, H81.8, H81.9, R42 with G63, E53.8, N95.1, G62, I951, H55 or F45.8), are at least 18 years old, and are mentally able to follow instructions. They must also be insured by the AOK Bayern. Patients will be excluded if they are suffering from a mental illness (e.g. dementia), or a terminal disease with a life expectancy of less than 12 months.

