**Fig. 1 Fig1:**
[figure not shown]
Summary of the process flow of the intervention. During the study period the German Center for Vertigo and Balance Disorders (DSGZ) will re-assess all patients for the purpose of validating the diagnosis and treatment. Further, the expert network will be established throughout the study period

Patients presenting with acute vertigo at the physician’s office will be eligible for inclusion in the study. After inclusion, the physician (family practitioner, neurologist, otorhinolaryngologist, internal specialist) will use the CCDS. The patient’s answers to a few basic questions (e.g. How long does the vertigo last?), symptoms (e.g. vomiting) and clinical findings (e.g. horizontal nystagmus) will be analysed by an AI-based algorithm. Subsequently suggestions are offered to the physician for a) a categorization of the possible underlying syndrome (e.g. peripheral vs. central vertigo), b) required diagnostic procedures, c) treatment options, and d) referral to physicians with a different medical speciality (e.g. referral from a family practitioner to a neurologist). Additionally, the physician will receive a warning message when symptoms of a severe underlying disease are noted (e.g. skew deviation in cerebral stroke).

Questionnaires and underlying decision algorithms are based on national and international guidelines and the International Classification of Vestibular Disorders (ICVD) of the Bárány Society.

After the diagnostic process has been completed, the patient is given access to a mobile application (app). This application informs the patient about the underlying disease, supports the therapeutic process and monitors the course of the disease. The app is personalized to the patient’s demographic data (age, gender, language, visual impairment) and to the diagnosis. Furthermore, patients will be instructed to fill out a vertigo/dizziness diary on a daily basis. A newly developed, AI-based algorithm then monitors the information gathered from the diary and correlates it with the individual disease. Additionally, an integrated video documentation and analysis system will analyse eye movements and gait abnormalities by the means of pattern recognition (e.g. neuronal networks, deep learning algorithms) [20–22]. It will be used to objectify the diagnosis and classify patient’s self-recorded symptoms.

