### Process evaluation

Process evaluation will be conducted according to the guidelines of the Medical Research Council (MRC) Framework for evaluating complex interventions [27]. During an initial 6-month pilot period, the acceptance and feasibility of the intervention and its components will be evaluated using a mixed-methods approach. In the following main trial (16 months of recruitment of patients) the processes and quality of the implementation will be evaluated. We will evaluate various aspects, including the structure and performance of the included practices, implementation fidelity, satisfaction with the intervention and implementation, assessment of scalability, and documentation and assessment of unexpected effects. Auditing will include quality parameters such as study protocol adherence and number of protocol violations, data quality, and adherence to data protection protocols.

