### Sample size

A difference of 6–10 points in the DHI with a standard deviation of 20 points is assumed to be a relevant clinical difference. This corresponds to an effect size of between 0.3 and 0.5 [6]. A two-sided t-test for independent groups with an effect size of 0.3, an alpha of 0.05 and beta of 0.20 (power = 80%) results in a sample size of *n* = 352 individuals. The inclusion of 10 patients per cluster was assumed with a drop-out rate of 10%, which corresponds to the drop-out rate of similar studies [28, 29]. Therefore, the inclusion of nine patients per cluster was assumed. Taking into account a conservative inter-cluster correlation coefficient (ICC) of 0.04 [30], a design effect (DE) of 1.32 was calculated (DE = 1 + (*k* – 1)  × ICC). This results in a sample size of *n* = 468 patients (234 in the intervention program and 234 in the standard care) and thus 52 clusters. At the level of the clusters, a drop-out rate of 2 clusters per study arm can be expected [31]. To further compensate for possible variations in patient recruitment of the clusters, two additional clusters per study arm were considered. Thus, a total of 60 clusters with 600 patients was calculated.

The additional 6-month pilot phase will include 10 clusters with an expected recruitment of 10 patients per cluster (total *n* = 100 patients; 50 for each study arm). The aim of the pilot phase is to gather information to optimize the study processes (recruitment, randomisation, data gathering, etc.) and to adapt/improve the CCDS and mobile application. The measured outcomes of the pilot phase will not be included in the evaluation and statistical analysis of the main study.

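### Patients are recruited after their practice has been randomised and knows its arm, and neither the stated concealment nor the stated blinding protects the DHI comparison from differential recruitment

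*Protocol article*

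**What the plan says.** All references are to the protocol article.

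- **Randomisation (Trial design).** Practices are allocated 1:1 "to either the intervention or the control group after inclusion into the main study". Stratification is by practice size.
- **Concealment (Trial design).** "Concealed allocation of participating practices will be implemented centrally by an independent person that has no knowledge of the practice identity". Nothing comparable is described for patients.
- **Patient entry (Participants).** "Consenting patients will be eligible for inclusion if they newly consult a participating practice for acute vertigo or dizziness". The Process evaluation section gives the period: "In the following main trial (16 months of recruitment of patients").
- **Knowledge of arm (Intervention, text with Fig. 1).** "After inclusion, the physician (family practitioner, neurologist, otorhinolaryngologist, internal specialist) will use the CCDS". The patient later receives the app and is told to keep a daily diary.
- **Blinding (Data collection procedures).** The only blinding described is of the three-month re-assessment at the specialist centre. Under Measures, that visit serves to judge diagnostic accuracy.
- **Outcome and size (Measures, Sample size).** The DHI is the primary patient-level effectiveness measure. About 10 patients per practice are expected: "The inclusion of 10 patients per cluster was assumed with a drop-out rate of 10" per cent.

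**The concern.** Randomising practices balances the practices, and through them the patients who consult there. It does not balance the patients who are enrolled if enrolment happens later and is handled by people who know the arm. Two things can then differ by arm: which eligible patients are asked, and which of those asked agree. Neither needs bad faith. A physician with a new diagnostic tool may think of the study more readily for puzzling cases, or for patients likely to cope with an app. The Discussion itself lists acceptability and usability of the app, and the needs of older people, as possible limitations.

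If enrolled patients differ in baseline severity or age, part of the later DHI difference reflects who was recruited and not what the programme did. This concerns the primary patient-level outcome. An enrolment record that was not kept at the time cannot be rebuilt later.

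**Working it through.** **Step 1. The order of events as stated.**

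| Event | When | Protection stated |
|---|---|---|
| Practice joins and is randomised | Before its patients are included | Central concealed allocation |
| Physician learns the arm | Once the intervention tools are in use (and, by inference, when they are absent in control practices) | None possible |
| Patient consults, is approached, consents | During the following 16 months | None stated |
| Specialist re-assessment | Three months after inclusion | Blinded to group and initial diagnosis |

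The concealment acts before the step at risk and the blinding acts after it.

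**Step 2. The plan's own figures.** A two-sided t-test with effect size 0.3, alpha 0.05 and power 80% needs 175.4, so 176 per arm, or 352. The design effect is 1 + (9 - 1) × 0.04 = 1.32. Then 352 × 1.32 = 464.6; 464.6 / 9 = 51.6, so 52 clusters and 52 × 9 = 468 patients, 234 per arm. Adding 4 + 4 clusters gives 60, with 60 × 10 = 600 patients. All stated figures reproduce, and none is disputed.

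**Step 3. Standard error of the DHI difference.** Inputs from Sample size: SD 20, 234 per arm, design effect 1.32.

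SE = 20 × √(2/234 × 1.32) = 20 × √0.01128 = 20 × 0.1062 = 2.12 points.

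**Step 4. Illustrative shift.** The documents give no baseline gap and no correlation, so both are assumed. Spurious shift = baseline gap × correlation of baseline with follow-up DHI. For a gap of 3 points and a correlation of 0.5 to 0.7, the shift is 3 × 0.5 = 1.5 to 3 × 0.7 = 2.1 points. For a gap of 5 points it is 2.5 to 3.5 points.

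**Step 5. False-positive rate when there is no true effect.** Noncentral t with 50 degrees of freedom (52 clusters minus 2), noncentrality = shift / SE, unadjusted comparison:

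| Shift (points) | Shift / SE | False-positive rate |
|---|---|---|
| 0 | 0 | 5.0% |
| 1.5 | 0.71 | 10.7% |
| 2.1 | 0.99 | 16.3% |
| 2.5 | 1.18 | 21.1% |
| 3.5 | 1.65 | 36.6% |

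**Step 6. Power if the shift runs against a true 6-point effect.** Normal approximation, power = Φ((6 - shift)/SE - 1.96). No shift: Φ(2.82 - 1.96) = 80.6%. Shift of 2: Φ(1.88 - 1.96) = 46.9%. Shift of 3: Φ(1.41 - 1.96) = 29.2%.

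**The case against.** The strongest reply is that the order is inherent. People who present acutely cannot be listed before their practice is allocated, and a condensed article may leave enrolment rules, logs and consent procedures to the full protocol. Both points stand. The finding therefore rests on the order that is stated, not on missing detail, and the remedy leaves that order alone. If the full protocol already holds these safeguards, citing them settles the matter.

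Four stronger readings are tempting, and the documents do not support them.

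- **Physicians pick 10 patients from a far larger pool.** The Background says that "over 9% of the adult population received a diagnosis of vertigo annually, most of these in primary care". Over 16 months that gives 0.09 × 16/12 = 0.12 diagnosed patients per insured adult. The article gives no practice size, no share of patients with the participating insurer and no share of new consultations. Assuming 500-2,000 adults, 20-50% with that insurer and 25-100% new, the pool runs from 500 × 0.20 × 0.12 × 0.25 = 3 to 2,000 × 0.50 × 0.12 × 1 = 120. It could be below 10. A large pool is not needed, because differential approach or consent is enough.
- **Each practice must recruit 10.** Sample size only assumes 10 and adds clusters for uneven recruitment.
- **Consent differs by arm because of the app and diary.** No section describes what consent contains or who obtains it.
- **The t-test in Sample size is the analysis.** It is a planning formula, and the article names no analysis model. Patient data are collected at inclusion, so baseline adjustment is possible and may be planned.

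The direction of bias is also open. Favouring difficult cases would raise DHI in the intervention arm, while favouring app-capable patients might lower it.

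The Harms section dates its reporting from the randomisation of the first patient, which might suggest individual allocation. Trial design and Sample size are cluster-based throughout, so that wording should be reconciled.

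**Conclusion.** The concern holds as a stated design risk. Followed as written, the plan recruits patients at practices that already know their arm, with concealment at the wrong level and blinding at the wrong time to protect that step.

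Its size is not known. The 11-16% false-positive rate for a shift of 1.5 to 2.1 points shows only that a shift of a quarter to about a third of the 6-point target (1.5/6 = 25%, 2.1/6 = 35%) would matter. It rests on an assumed 3-point baseline gap, an assumed correlation of 0.5 to 0.7, and an unadjusted comparison that the article does not specify. Adjustment would reduce the effect of measured differences but not of unmeasured ones. The article gives no evidence that selective recruitment will occur, or which arm it would favour.

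**What to change.** Keep the order of randomisation and add the following, identically in both arms, before the first patient is included:

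1. Approach every eligible patient consecutively, with no cap at 10, so that busy practices can still offset slow ones.
2. Keep a short anonymised log of eligible patients not enrolled, with the reason.
3. Use the same consent wording.
4. Complete the baseline DHI before any arm-specific material is shown.
5. Include baseline DHI and age as covariates in the primary DHI analysis, if the SAP does not already do so.
6. Report enrolled/eligible fractions and baseline characteristics by arm.

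Where the full protocol already contains any of these, a reference to it is enough.

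The cost is a small extra workload for practices to keep the log. Patient data are already collected at inclusion; the article does not list the DHI among them by name, so that should be confirmed. What remains is possible bias from unmeasured differences. The log and the reported fractions would help readers to judge it but would not remove it.

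### It is unclear whether specialist-only practices are randomised; if they are, specialty is a plausible prognostic cluster-level factor that the allocation, stratified by practice size alone, leaves to chance

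*Protocol article*

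**What the plan says.** On allocation, the Trial design section states that "Clusters will be randomly assigned in a balanced 1:1 block design to either the intervention or the control group", and then: "The size of the practice (number of patients per year) will be considered as a stratification factor". No other balancing factor is named anywhere in the article.

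On what a cluster is, the sections do not agree:

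- Trial design: "Clusters will be primary care practices in Bavaria", and "Practices with special focus on vestibular or balance disorders will be excluded".
- Participants, first sentence on clusters: "Practices in Bavaria will be eligible if they are led by at least one primary care physician".
- Participants, next sentence: because patients may go straight to a specialist, "neurologists, otorhinolaryngologists and internal medicine specialists will be included in addition to family practitioners".
- Intervention, text following Fig. 1: "the physician (family practitioner, neurologist, otorhinolaryngologist, internal specialist) will use the CCDS".
- Measures: the provider-level effectiveness outcome is the accuracy of the primary care physician's diagnosis, checked by re-assessment at the tertiary centre.

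The Sample size section plans 60 clusters, "Taking into account a conservative inter-cluster correlation coefficient (ICC) of 0.04". It does not state how many clusters are expected to be specialist practices, and no DHI or accuracy figure is given by specialty.

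**The concern.** If neurology, ENT and internal medicine practices are clusters in their own right, the trial randomises units that may differ in baseline skill with vertigo, in the route by which patients reach them and in case mix. The article's own Background points this way for diagnosis. It says that most syndromes can be diagnosed and managed by specialists who have interdisciplinary training, whereas primary care physicians find vertigo complex. Diagnostic accuracy is the provider-level outcome, so a difference in the specialist share between arms bears on it directly.

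With about 30 clusters per arm, a noticeable imbalance in such a factor is quite likely unless the allocation prevents it. An analysis model can adjust for the imbalance, but it cannot restore balance once practices are allocated. The allocation scheme is fixed in this document, so the point is not one that can wait for an analysis plan.

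**Working it through.** **1. The plan's own sample size reproduces.** A two-sided t-test with a difference of 6, SD 20, alpha 0.05 and power 80% needs 176 per arm, or 352 in total. The design effect is 1 + (9 − 1) × 0.04 = 1.32. Then 352 × 1.32 = 464.6, and 464.6 / 9 = 51.6, so 52 clusters × 9 = 468 patients. Adding 4 clusters for drop-out and 4 for variable recruitment gives 60 clusters, and 60 × 10 = 600 patients. Power at 468 patients is 80.6% (normal approximation).

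**2. Chance imbalance in specialty.** Inputs: 60 clusters, 30 per arm (from the document), and K specialist practices (assumed, since no share is given). If allocation ignores specialty, the number X of specialist practices in one arm is hypergeometric (60, K, 30). The between-arm difference in specialist share is (2X − K)/30, with SD = 2 × √(s(1 − s)/59), where s = K/60. For s = 0.5 this is 2 × √(0.25/59) = 0.130.

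**3. What this does to the DHI contrast.** If specialist and family practices differ by g points in mean DHI (g assumed), the chance shift has SD = g × SD of the share difference.

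| Assumed share (K) | SD of share difference | P(≥10 points) | P(≥20 points) | SD of shift, g = 5 | SD of shift, g = 10 |
|---|---|---|---|---|---|
| 10% (6) | 0.078 | 20% | 2% | 0.39 | 0.78 |
| 20% (12) | 0.104 | 33% | 10% | 0.52 | 1.04 |
| 30% (18) | 0.119 | 40% | 16% | 0.60 | 1.19 |
| 40% (24) | 0.128 | 43% | 19% | 0.64 | 1.28 |
| 50% (30) | 0.130 | 44% | 20% | 0.65 | 1.30 |

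The probability columns refer to percentage points of specialist share; the last two columns are DHI points.

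**4. The ceiling set by the plan's ICC.** With ICC 0.04 and SD 20, the between-cluster variance is 0.04 × 400 = 16 (SD 4). A two-group specialty gap contributes s(1 − s)g², so g can be at most 4/√(s(1 − s)): 13.3 points at a 10% share, 10 at 20% and 8 at 50%. At that ceiling the SD of the chance shift is 2 × √(s(1 − s)/59) × 4/√(s(1 − s)) = 8/√59 = 1.04 points, whatever the share. Table entries above 1.04 therefore require more between-cluster variance than the plan assumes.

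**5. What balancing and adjusting could gain.** If the ICC of 0.04 already includes specialty, and specialty explains a fraction f of the between-cluster variance, the residual design effect is 1 + 8 × 0.04 × (1 − f). For f = 25%, 50% and 100% this is 1.24, 1.16 and 1.00, and power at 468 patients is 83%, 85% and 90%, against 80.6% without adjustment.

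**The case against.** **The premise is unsettled.** If every cluster must be led by a primary care physician, specialist-only practices may not be clusters, and the mix is narrower than the list of specialties suggests. This stands. It is why reconciling the sections comes first and the rest is conditional.

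**How strongly specialty matters is not documented.** A reader might infer that specialty is the dominant cluster-level determinant of diagnosis and outcome. The article does not support that. It ranks no determinants. Its remark on specialists concerns those with interdisciplinary training, it criticises the narrow view of single disciplines, and it excludes practices with a vestibular focus. A plausible prognostic factor is as far as the text goes.

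**Chance imbalance is not bias.** A reader might infer that an uneven split biases the result. Randomisation remains unbiased in expectation, and variation between clusters is what the design effect allows for. What is lost is precision, and the credibility of a comparison with visibly different arms.

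**Power is not shown to fall.** A reader might compute a loss by adding specialty variance to the ICC. With 15 of 60 clusters specialist, 0.25 × 0.75 × g² is 4.7 for g = 5 and 18.75 for g = 10. The ICC becomes (16 + 4.7)/(400 + 4.7) = 0.051 or (16 + 18.75)/(400 + 18.75) = 0.083. With 26 clusters per arm and a t-test on 50 degrees of freedom, power goes from 79% to 76% or 67%. But nothing shows that 0.04 excludes specialty; if it already includes it, power stays as planned. The larger addition exceeds the plan's whole between-cluster variance of 16. The calculation also uses the minimum number of clusters: with 28 per arm after the expected drop-out, the same method gives 82% at 0.04 and 79% at 0.051.

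**Adjustment may be planned elsewhere.** An analysis plan that is not shown may include specialty as a covariate, which could recover much of the precision. That is fair, but adjusting for a poor split is weaker than preventing it, especially with few specialist clusters.

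**Conclusion.** Two things hold. First, the Trial design, Participants and Measures sections do not settle whether specialist-only practices are randomised, and they must be reconciled, because this determines both the units and the population of the trial. Second, if such practices are randomised, a plausible prognostic factor is left out of an allocation that names only practice size.

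In size, this is a matter of precision and credibility, not validity. An imbalance of at least 10 percentage points is fairly likely (about one in five to just over two in five), but its typical effect on the DHI contrast is modest against the 6-point target, and at most about 1.04 points (SD) under the plan's own ICC. The effect on diagnostic accuracy may matter more but cannot be quantified from the document.

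These figures rest on assumed specialist shares of 10–50%, assumed DHI gaps of 5–10 points, and allocation unrelated to specialty. If practice size happens to track specialty, stratifying by size would already remove part of the imbalance. The stated sample size is unaffected.

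**What to change.** 1. Reconcile the sections: say whether neurology, ENT and internal medicine practices without a leading primary care physician are clusters. If they are, correct the cluster definition and the wording of the provider-level outcome. If they are not, remove or reword the sentence that adds them.
2. If they are, then before the first practice is allocated, stratify by specialty (family practice or specialist) crossed with two practice-size classes, giving four blocked strata.
3. Include both factors in the outcome models, for diagnostic accuracy as well as the DHI.

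The cost is a revised randomisation list, one additional model term and a few incomplete blocks. Short blocks keep the last of these small. With blocks of two, for example, each stratum can be off by at most one practice, so the two specialist strata together by at most two, or 2/30 = 6.7 percentage points. The required sample size does not change at an ICC of 0.04.
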